## Abstract

**Background:**

Pressure in combination with shear forces can deform soft tissues and lead to development of pressure ulcers. The prevalence rate of pressure ulcers in the United Kingdom remains unacceptably high and can occur across the human lifespan. The posterior heel represents a common anatomical site for pressure ulcers due to soft tissues lying adjacent to bony prominences and being exposed to pressure and shear during lying postures. Localized cooling and interface materials that reduce shear may offer potentially therapeutic benefits in the development of pressure ulcers. Yet the physiological mechanisms underpinning the potential benefits of localized cooling are not fully understood.

**Objective:**

This study protocol aims to investigate how localized cooling influences the skin’s microvascular, inflammatory, structural, and perceptual tolerance to repeated shear loading at the heel.

**Methods:**

The protocol will be tested on individuals of different age, sex, skin tone, and comorbidities, using a repeated measures design. Three cohorts will be recruited: (1) young and healthy (n=35), (2) older and healthy (n=35), and (3) with spinal cord injury (n=35). Participants will complete 3 testing sessions using a custom-built shearing rig with integrated thermal plate, during which the posterior aspect of the heel will be exposed to a standardized mechanical stimulus to elicit repeated pressure and shear loading. The experimental condition of each session will be determined by the temperature of the thermal plate, which will be set to either 36 °C (no cooling), 24 °C (mild cooling), or 16 °C (strong cooling). Continuous measurements will include kinetic coefficient of friction (CoF) and skin blood flow (via laser Doppler flowmetry; 40 Hz). Pro- and anti-inflammatory biomarkers in skin sebum (via Sebutape), structural skin properties (via optical coherence tomography), skin conductance (in microsiemens) and ratings of thermal sensation, comfort, and acceptance (via Likert scales) will also be assessed before and after the shear stress protocol.

**Results:**

Recruitment began in January 2024. As of February 2025, 43 participants had been enrolled in the study. Data collection and analysis are ongoing, and published findings are expected to be available in early 2026.

**Conclusions:**

This analysis will help identify mechanisms of skin damage following repeated shear stress at the heel, furthering our understanding of superficial pressure ulcers. It will also establish physiological and perceptual thresholds for the protective effects of cooling from shearing-induced damage at the heel.

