It is also important to note that physiological and perceptual tolerance to pressure and shear at the skin interface may also vary as a function of age and comorbidities [30], which could in turn diminish the therapeutic efficacy of cooling. For example, aging-induced changes in skin biophysics and morphology [31], as well as decreases in both reflex cutaneous vasoconstriction and density of thermoreceptors [32], are likely to modulate the thermoregulatory and perceptual sensitivity of the skin to localized cooling. Similarly, autonomic and sensory dysfunctions resulting from SCI manifest in impaired control of skin blood flow and lack of sensation below the injury level [33,34].

Based on the evidence above, this study protocol aims to investigate (1) how different levels of localized cooling influence the skin’s microvascular, inflammatory, structural, and perceptual responses to repeated pressure and shear loading at the heel; and (2) how metabolic, immunological, biophysical, and perceptual pathways underlying the effects of localized cooling on skin tolerance to shear are modulated by aging and SCI. The research that will be delivered via this protocol will be both important in improving scientific knowledge and timely to societal demands, as it will support the development of user-centered approaches to maintaining skin tissue viability via evidence-based therapeutic cooling.

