## Methods

### Overview

Participants will attend 3 experimental sessions separated by a minimum of 24 hours in the Clinical Academic Facility located at Southampton General Hospital (Southampton, United Kingdom). During the sessions, participants will place the center of their posterior heel on a custom-built friction rig with an integrated thermal plate to undergo a standardized protocol eliciting repeated pressure and shear force. The study will use a randomized crossover design involving 3 plate temperatures: 36 ºC (no cooling), 24 ºC (mild cooling), or 16 ºC (strong cooling). Microclimate conditions at the interface between a loaded skin site at risk of pressure ulcer (eg, the sacrum) and a support surface (eg, a mattress) are commonly associated with skin temperatures of approximately 38 ºC. Following pilot testing, some participants (n=2) found a 38 ºC plate temperature to be borderline uncomfortable, so we decided to reduce the plate temperature to 36 ºC to improve thermal tolerability in the no cooling condition. The rationale for using 2 levels of cooling was 2-fold: first, prior research investigating localized cooling on tissue viability in animal models [17,18] used cooling interventions at 25 ºC, demonstrating the benefit of reduced skin temperature in preserving tissue viability. Second, one of the main aims of the study is to examine how different levels of cooling may influence the biophysical properties of the skin and perceptual thermal tolerances of both mild (24 ºC) and strong (16 ºC) cooling.

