The protocol starts by participants placing the heel in the center of the thermal plate over the hole, where the LDF optical probe is located flush to the surface. Positioning of the bed and lower limb will be modified to provide a standardized 15-N axial load on the plate. Skin blood flow will be measured intermittently (accounting for displacement of the heel following the static loading phases) throughout the protocol via LDF (moorVMS-LDF laser Doppler monitor; Moor Instruments). The heel will remain in place for a 60-second thermal preconditioning period to allow for temperature adaptation at the skin interface (at 36 °C, 24 °C, or 16 °C). The repeated shearing sequence will then commence (Figure 2), initially with a 10-second pause, before the servomotor travels in one direction pulling the rig and displacing it by 10 cm, pausing for 1 second, then traveling in the opposite direction, pushing the rig back to the original starting point. This sequence completes one repetition, which is repeated 10 times. After completing the 10 shearing repetitions, participants’ thermal perceptions will be recorded, followed by posttest OCT, skin sebum, and skin conductance measurements.

The sections below provide a description of the measurements to be used during the protocol.

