### Statistical Analyses

Data will be assessed for normality of distribution with the Kolmogorov-Smirnov test. Within- and between-subject mean differences (n=35 with 95% CIs) as a function of mechanical stimulus temperature (ie, 36 ºC, 24 ºC, and 16 ºC), time (ie, varying levels depending on the variables’ sampling rate), and participant group (ie, young, older, SCI) will be analyzed. These independent and interactive effects will be assessed by means of 3-way mixed model ANOVAs (or Friedman tests) for biomarker expression, skin structural properties, biophysical properties (ie, imaging parameters), subjective thermal perceptions, and kinetic CoF. Post hoc analyses will be performed between shear stimulus temperatures, time, and participant groups based on the presence of main effects and using the Tukey test. Group-related covariables associated with sex, skin tone, and clinical status (applicable to SCI participants only) will be considered in all analyses to interpret the proportion of variance unexplained by the main effects (ie, temperature, time, and group) and their interactions.

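### The abstract promises cooling thresholds, but three fixed plate temperatures and the stated analysis can only bracket a threshold within a 12 °C or 8 °C gap, or leave it somewhere below 16 °C

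*Protocol article*

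**What the plan says.** The claim stands in the Conclusions of the abstract, without qualification: "It will also establish physiological and perceptual thresholds for the protective effects of cooling from shearing-induced damage at the heel".

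The design is described in three places:

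- The Methods paragraph of the abstract says of the plate temperature: "which will be set to either 36 °C (no cooling), 24 °C (mild cooling), or 16 °C (strong cooling".
- Methods, Overview: "The study will use a randomized crossover design involving 3 plate temperatures".
- Experimental Procedures (text after Figure 2): the heel rests on the plate for a "60-second thermal preconditioning period to allow for temperature adaptation at the skin interface (at 36 °C, 24 °C, or 16 °C", and then the shear repetitions begin. Each session has one temperature. No ramp and no intermediate level is described.

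The aims are more modest than the concluding sentence. The Introduction asks "how different levels of localized cooling influence the skin’s microvascular, inflammatory, structural, and perceptual responses" to loading. The Overview gives as one reason for two cooling levels the wish to "examine how different levels of cooling may influence the biophysical properties of the skin and perceptual thermal tolerances" under mild and strong cooling. The Objective in the abstract speaks only of how cooling influences tolerance to shear.

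Statistical Analyses plans mean differences with 95% confidence intervals by temperature, time and group. It continues: "These independent and interactive effects will be assessed by means of 3-way mixed model ANOVAs (or Friedman tests" for most outcomes, and then: "Post hoc analyses will be performed between shear stimulus temperatures, time, and participant groups", using the Tukey test.

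**The concern.** A threshold for a protective effect is the temperature at which protection begins. A perceptual threshold is the temperature at which sensation or comfort changes. Finding either requires observing the response on both sides of the change, closely enough to say where it lies. A comparison of three widely spaced levels answers a different question, namely whether the response at one level differs from that at another.

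What is at stake is the study's stated conclusion. If the sentence in the abstract is carried into the results paper, a figure such as 24 °C or 16 °C could be reported as an established threshold when it is only one of the temperatures chosen in advance. The uncertainty about where the change occurs would span the gap between tested levels, and the planned analysis would not show it.

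**Working it through.** The plan gives no threshold figure to reproduce. The check is whether the stated design can identify a threshold at all.

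**Inputs.** Tested levels: 36, 24 and 16 °C (abstract, Methods; Methods, Overview). Delivery: one fixed temperature per session (Experimental Procedures). Analysis: temperature as a three-level factor with pairwise post hoc comparisons (Statistical Analyses).

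**Step 1: gaps between adjacent levels.**

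- 36 − 24 = 12 °C
- 24 − 16 = 8 °C
- whole range: 36 − 16 = 20 °C

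**Step 2: can the three levels tell thresholds apart?** Suppose the effect is absent above a threshold *t* and present at or below it, and read the response without error at the three levels (0 = no effect, 1 = effect).

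| True threshold *t* (°C) | at 36 °C | at 24 °C | at 16 °C |
|---|---|---|---|
| 24.1, 30 or 35.9 | 0 | 1 | 1 |
| 16.1, 20 or 23.9 | 0 | 0 | 1 |
| 15.9 or 10 | 0 | 0 | 0 |

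Every value within a row gives the same pattern, even with no sampling error. The data separate the three rows and nothing within a row. The first row is the 12 °C interval and the second is the 8 °C interval. The third has no lower limit.

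**Step 3: does the stated analysis add information?** A factor with three levels estimates three means and their differences. It says nothing about temperatures in between. A curve could, but a two-parameter curve fitted to three levels leaves 3 − 2 = 1 degree of freedom to check its shape, and a three-parameter curve leaves 3 − 3 = 0. No such curve is described.

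**Step 4: does another measurement fill the gap?** Ethical Considerations mentions skin temperature monitoring as a safety measure, and the rig records plate surface temperature. No analysis uses either as a continuous exposure. Perceptual ratings are taken only before and after the shear protocol.

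**Scale.** The number of equally spaced levels needed over 16–36 °C for a gap of at most *g* is ceil(20/*g*) + 1. This gives 4 levels for 8 °C, 5 for 5 °C, 6 for 4 °C and 11 for 2 °C. These figures show how resolution depends on the number of levels. They are not a proposal to add conditions.

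**The case against.** **It is one sentence.** The threshold claim appears as a deliverable only in the Conclusions of the abstract. The Objective, the aims in the Introduction, the rationale in the Overview, Statistical Analyses and the Discussion do not make it. This stands, and it limits the point to the wording of one conclusion. The choice of three temperatures is not at fault.

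**A model could place a threshold inside a gap.** Several outcomes are continuous, such as the coefficient of friction, blood flow and biomarkers. A fitted or interpolated curve would give a point estimate. This also stands, so it would be wrong to say that no finer resolution is possible under any analysis. The estimate would rest on the assumed shape, however. As an illustration with assumed responses of 0, 0.3 and 1 at 36, 24 and 16 °C, linear interpolation puts the half-maximal response at 24 − (0.5 − 0.3)/(1 − 0.3) × 8 = 21.7 °C. Other monotone curves through the same three points cross 0.5 anywhere between 24 and 16 °C.

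**The word may be meant loosely.** If threshold means which tested level is protective and still acceptable, the design can answer that. This is a fair reading, but the article does not define the word that way, and the result would be a comparison of levels.

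**Stronger readings a reader might infer.** One is that the plan would call the first statistically significant temperature the threshold, so that the threshold would move with sample size or differ between groups through precision alone. No section states such a rule, and Statistical Analyses already plans mean differences with confidence intervals. Another is that a threshold figure is promised for use in cooling devices. The Introduction and the Discussion speak of patient-centred approaches, and the Discussion names device manufacturers among its readers, but neither ties a threshold temperature to a device.

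**Conclusion.** The point holds as a mismatch between one stated conclusion and the stated design and analysis. Without an assumed dose-response shape, a threshold can be placed only within 24–36 °C (12 °C wide), within 16–24 °C (8 °C wide), or below 16 °C. More participants would make the three means more precise but would not narrow these intervals. The bracketing itself assumes that the effect does not reverse as the plate gets colder.

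The comparison of the three temperatures is sound, and the objective and aims claim no threshold. A fuller analysis plan, if there is one, might add a curve, but three levels would still barely test its shape. The conclusion therefore does not depend on detail that an article may leave out.

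**What to change.** Reword the sentence in the abstract's Conclusions to match the aims in the Introduction and the rationale in the Overview. For example: the study will compare the physiological and perceptual effects of two cooling levels, 24 and 16 °C, with a 36 °C reference.

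If a threshold statement is kept, two conditions apply:

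- Report it only as the interval between tested levels, for example between 16 and 24 °C, and say that it refers to plate temperature.
- Base it on the mean differences with 95% confidence intervals already planned, for 24 versus 36 °C and for 16 versus 24 °C. Where the interval for 24 versus 36 °C is too wide to say whether 24 °C has an effect, the bracket is the whole 16–36 °C range (20 °C).

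The article reports data collection and analysis as ongoing, so the wording can be settled before the findings are published. No new data, sessions or participants are needed. The cost is a less favourable conclusion.

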**International Registered Report Identifier (IRRID):**

DERR1-10.2196/73250

## Introduction

Pressure ulcers constitute a type of localized damage to the skin and/or underlying soft tissue resulting from prolonged periods of pressure or pressure in combination with shear forces [1]. In the United Kingdom alone, the annual cost of treating chronic wounds, including pressure ulcers, has been estimated to be approximately £8.3 billion (US $12.7 billion) [2]. Accordingly, an improved understanding of the fundamental mechanisms underlying the physiological tolerance of human skin to mechanical loading and shearing could lead to the development of cost-effective, personalized solutions to prevent these wounds and improve patient care and quality of life [3].

Sustained localized mechanical loading and shearing of the skin can arise from lying and sitting postures, particularly in individuals with mobility impairment such as spinal cord injury (SCI) [4]. Internal tissue deformations occur as a result of sustained pressure and shear forces that can lead to changes in the physiology of skin and subdermal tissue, including ischemia in the blood vasculature, lymphatic impairment, and direct deformation damage [5,6]. It has been reported that nearly 30% of pressure ulcers occur at the heel, with this region being the second most likely area for pressure damage after the sacrum [7,8]. As opposed to the thick skin of the plantar heel, the posterior heel has thin, striated skin [9], which is very susceptible to pressure- and shear-induced damage [10]. Yet the mechanisms underlying the elevated risk of shear-induced damage at the heel remain under-studied.

Microclimate conditions within and around skin tissues strongly influence the tolerance of the skin to mechanical loading and shear [11]. For example, elevated temperature and humidity at the skin interface reduce the mechanical stiffness and strength of the skin [12] while also increasing its coefficient of friction [13]. These mechanisms can lead to a greater risk of tissue damage for the same mechanical stress [14,15]. In contrast, cooling reduces skin tissue’s metabolic demands and could increase the skin’s physiological tolerance to mechanical loads [12,16]. Early animal studies revealed that reduced skin temperature minimizes the risk of pressure ulcer formation [17,18]. This may occur through altered microvascular responses [18], as well as via downregulation of the expression of pro-inflammatory cytokines such as tumor necrosis factor α (TNFα), which is mediated by the stimulation of cold-sensitive transient receptor potential melastatin 8 (TRPM8)–expressing neurons in dorsal root ganglia [19,20]. Furthermore, our preliminary proof-of-concept experimental and modeling data on a representative skin site (the finger) indicated that skin cooling to 16 ºC can reduce friction by up to 35% for the same mechanical load [13]. This effect is likely due to changes in the viscoelastic properties of cooled skin tissues, which could in turn translate to reductions in shear stress. While this evidence highlights the potential therapeutic role of skin cooling for protecting tissue health, the mechanisms by which cooling enhances skin tolerance to pressure, shear, and friction remain poorly understood in humans [17-19,21-24].

In addition to its physiological effects, localized cooling of the skin can induce cold discomfort, which can limit acceptability and adherence to therapeutic interventions that promote skin integrity, particularly for vulnerable individuals at risk of pressure ulcers [25]. However, evidence on how the absolute temperature of a surface shearing against the skin contributes to thermomechanical discomfort is limited [26]. While the evidence above highlights the field’s limited mechanistic understanding of the effects of skin cooling on skin tissue viability, commercially available microclimate management systems, which deliver local and full-body cooling, continue to be developed and applied to support pressure ulcer prevention [27-29].

It is also important to note that physiological and perceptual tolerance to pressure and shear at the skin interface may also vary as a function of age and comorbidities [30], which could in turn diminish the therapeutic efficacy of cooling. For example, aging-induced changes in skin biophysics and morphology [31], as well as decreases in both reflex cutaneous vasoconstriction and density of thermoreceptors [32], are likely to modulate the thermoregulatory and perceptual sensitivity of the skin to localized cooling. Similarly, autonomic and sensory dysfunctions resulting from SCI manifest in impaired control of skin blood flow and lack of sensation below the injury level [33,34].

Based on the evidence above, this study protocol aims to investigate (1) how different levels of localized cooling influence the skin’s microvascular, inflammatory, structural, and perceptual responses to repeated pressure and shear loading at the heel; and (2) how metabolic, immunological, biophysical, and perceptual pathways underlying the effects of localized cooling on skin tolerance to shear are modulated by aging and SCI. The research that will be delivered via this protocol will be both important in improving scientific knowledge and timely to societal demands, as it will support the development of user-centered approaches to maintaining skin tissue viability via evidence-based therapeutic cooling.

## Methods

### Overview

Participants will attend 3 experimental sessions separated by a minimum of 24 hours in the Clinical Academic Facility located at Southampton General Hospital (Southampton, United Kingdom). During the sessions, participants will place the center of their posterior heel on a custom-built friction rig with an integrated thermal plate to undergo a standardized protocol eliciting repeated pressure and shear force. The study will use a randomized crossover design involving 3 plate temperatures: 36 ºC (no cooling), 24 ºC (mild cooling), or 16 ºC (strong cooling). Microclimate conditions at the interface between a loaded skin site at risk of pressure ulcer (eg, the sacrum) and a support surface (eg, a mattress) are commonly associated with skin temperatures of approximately 38 ºC. Following pilot testing, some participants (n=2) found a 38 ºC plate temperature to be borderline uncomfortable, so we decided to reduce the plate temperature to 36 ºC to improve thermal tolerability in the no cooling condition. The rationale for using 2 levels of cooling was 2-fold: first, prior research investigating localized cooling on tissue viability in animal models [17,18] used cooling interventions at 25 ºC, demonstrating the benefit of reduced skin temperature in preserving tissue viability. Second, one of the main aims of the study is to examine how different levels of cooling may influence the biophysical properties of the skin and perceptual thermal tolerances of both mild (24 ºC) and strong (16 ºC) cooling.

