### Experimental Procedures

The study uses a repeated measures cohort design. Once participants have been screened and recruited, they will be invited to their randomly allocated experimental sessions [37]. They will come to the laboratory wearing comfortable, loose-fitting attire. Upon arrival, participants will be seated while they acclimatize to the ambient conditions of the laboratory (21-24 °C; 50% relative humidity) before recording height and body mass (Seca 874; Seca GmbH).

Following the pre-experimental checks, participants will be seated on a hospital bed in a semireclined position supported by pillows and a back rest. An elevated ankle cushion (20 × 11 × 10 cm) will then be positioned under the right leg and placed under the gastrocnemius muscle belly. To standardize the position of the foot and ankle and minimize movement during the repeated shear movements, an adjustable orthotic ankle foot brace will be strapped on to the right foot and the ankle angle set to a neutral plantar grade position (90°). This will ensure the skin over the calcaneus is consistently in contact with the surface of the thermal plate when the heel is placed on the friction rig and provide a constant relative tension in the local skin site (Figure 1). The axial load will then be standardized to exert 15 N of normal force on the thermal plate.

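### The stated model for a three-session crossover on one heel has no session-number (period) term, so any session drift costs precision or shifts the realised temperature contrasts

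*Protocol article*

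**What the plan says.** The Overview describes the design: "The study will use a randomized crossover design involving 3 plate temperatures". On spacing it says: "Participants will attend 3 experimental sessions separated by a minimum of 24 hours". Experimental Procedures fixes the side, since "an adjustable orthotic ankle foot brace will be strapped on to the right foot", so the same heel is sheared in every session. On allocation it says only that "they will be invited to their randomly allocated experimental sessions", with a literature reference. Whether the six possible orders are balanced is not stated.

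Statistical Analyses then names the model: "These independent and interactive effects will be assessed by means of 3-way mixed model ANOVAs (or Friedman tests". Its terms are "the main effects (ie, temperature, time, and group) and their interactions". Time is tied to how often each variable is sampled, so it means points within a session and not session 1, 2 or 3. Sex, skin tone and (for SCI) clinical status are the listed covariables. Session number and order appear nowhere.

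**The concern.** In a crossover, the order of conditions is what is randomised, and the session in which a condition falls is a known source of variation. Here one heel goes through ten shear repetitions and two tape samplings per session, possibly only a day apart, and the participant rates comfort each time. Some change from session 1 to session 3 is plausible, although the document neither measures nor reports any.

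If the orders are balanced, such drift leaves the temperature estimates alone but stays in the error term, so intervals are too wide and tests conservative. If the orders are unbalanced, part of the drift is carried into the temperature differences actually observed. Either way, the study loses information that a single model term would recover.

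**Working it through.** **The plan's own figure.** Participants gives a minimum of 18 per group, a target of 35 and up to 50% dropout. 18 / (1 − 0.5) = 36, and 35 × 0.5 = 17.5, so 35 is consistent to within one participant. The inputs behind the 18 are in the companion protocol and cannot be checked here.

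**Assumptions.** Residual SD is 1, participant effects are removed, and session effects are −d, 0 and +d. The drift d is in residual SDs per session, so session 1 to session 3 is 2d. The document gives neither d nor an SD.

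**Balanced orders.** The drift adds a sum of squares of 2d² per participant. Without a session term the error df are 2n − 2, so the expected residual variance is 1 + 2d²n/(2n − 2) = 1 + d²n/(n − 1), or about 1 + d².

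| d per session | session 1 to 3 | 1 + d² | SE ratio |
|---|---|---|---|
| 0.25 | 0.5 | 1.06 | √1.0625 = 1.03 |
| 0.5 | 1.0 | 1.25 | √1.25 = 1.12 |
| 1.0 | 2.0 | 2.00 | √2 = 1.41 |

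At d = 0.5 the effective sample is 1/1.25 = 80% of what it could be.

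A simulation (1,500 runs per setting) agrees. At n = 18 the SE of a contrast is 0.34, 0.37 and 0.48 without the term, against 0.33 with it; theory gives √(2/18) = 0.33. Power for an assumed difference of 0.7 SD within one cohort was:

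| n | d | without | with |
|---|---|---|---|
| 18 | 0.25 | 52% | 54% |
| 18 | 0.5 | 43% | 52% |
| 18 | 1.0 | 21% | 54% |
| 35 | 0.5 | 80% | 83% |
| 35 | 1.0 | 62% | 83% |

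Type I error without the term at n = 18 falls to about 3% at d = 0.5 and 0.4% at d = 1.0.

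**Simple random orders.** For one participant, the session positions of two temperatures differ by ±1 in four of the six orders and by ±2 in two. The variance is (4 × 1 + 2 × 4)/6 = 2, so the mean difference over n participants has SD √(2/n): 0.33 sessions at n = 18 and 0.24 at n = 35. The simulated 95th percentiles of its absolute value are 0.67 and 0.46. The contrast shifts by d times that difference. At d = 0.5 this reaches 0.5 × 0.67 = 0.33 SD (n = 18) or 0.5 × 0.46 = 0.23 SD (n = 35) in about 1 of 20 allocations, roughly one SE in each case. Pooled over three cohorts, the SD of the position difference is smaller: √(2/54) = 0.19 to √(2/105) = 0.14.

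Over repeated randomisation these shifts average to zero. Type I error stays near 5% (5.2% at d = 0.5 and 5.7% at d = 1.0, n = 18).

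**Which contrasts are exposed.** Write pre = session shift + error, and post = session shift + response to shear + error. In post − pre the additive session shift cancels. Biomarkers, OCT and skin conductance are taken before and after shear in each session, so their temperature-by-time contrast is protected unless the response itself changes over sessions. Their temperature main effect, averaged over pre and post, is not. Kinetic CoF exists only during shearing, so its temperature comparison has no pre-shear value to subtract.

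**The case against.** The strongest objection is that this is a condensed article with one paragraph on analysis, and a period term is often left to an analysis plan. That carries some weight, but the section lists the factors and the covariables, calls the analysis 3-way, and offers a Friedman alternative that has no place for session. As written, the model does not match the design.

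Three stronger readings are tempting, and the document supports none of them:

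- **That the temperature effects are biased or false positives inflated.** Randomised order prevents this on average. With balanced orders the tests are conservative.
- **That the orders are unbalanced.** The allocation method is given only by reference and may well be balanced. What can be said is that balance is not stated, that 35 does not divide by 6, and that up to 50% dropout could disturb any balance achieved.
- **That the cytokine results are compromised to the extent of the table above.** Those percentages do not apply to a before-after change under an additive shift.

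It is also fair to say that the drift is hypothetical. A value of 0.5 per session means a full residual SD between the first and last sessions, the 24 hours is a minimum gap, and at 0.25 per session the loss is about 3% or less.

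**Conclusion.** The point holds as a matter of precision, not validity. A crossover with three sessions on one heel is to be analysed by a model that omits session number. If drift is 0.5 residual SD per session and orders are balanced, SEs for exposed contrasts are about 12% larger than necessary, equal to losing a fifth of the sample. At 0.25 the cost is about 3%, at 1.0 about 41%, and with no drift there is none. With unbalanced orders, the realised contrasts also move by the drift times the imbalance.

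These figures rest on an assumed linear drift common to all participants. They apply chiefly to kinetic CoF, to temperature main effects, and to outcomes whose response to shear changes from session to session.

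**What to change.** Fit the analyses as linear mixed models with session number (1 to 3) as a fixed factor alongside temperature, time and group. Where normality fails, use a transformation, or a rank-based or ordinal mixed model that can hold the session term, instead of the Friedman test. State how orders are allocated. If they are not already balanced, allocate the six orders in blocks within cohort for those still to be recruited: 105 − 43 = 62 at the February 2025 count, though fewer may now remain.

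The cost is 2 df (34 to 32 for a single cohort of 18) and a mixed model in place of classical ANOVA or Friedman. No extra participants are needed. If there is in fact no drift, the term costs essentially nothing with balanced orders. With simple random orders it raises the SE by about 3% at n = 18 (0.330 to 0.341) and 2% at n = 35 (0.238 to 0.242).
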